### Participant eligibility, inclusion and exclusion criteria

Eligible participants are between 21 and 60 years of age with a diagnosis of Alcohol Use Disorder according to DSM-5. Further, they need to be abstinent after detoxification for at least 5 days. All participants must have the ability to provide fully informed consent and to use self-rating scales. Hence, they also need to have a sufficient understanding of the German language.

Participants will be excluded if they have a lifetime history of DSM-5 bipolar or psychotic disorder, or substance dependence other than alcohol or nicotine dependence; a current threshold DSM-5 diagnosis of a current (hypo)manic episode, major depressive disorder, generalized anxiety disorder, posttraumatic stress disorder (PTSD), borderline personality disorder, or obsessive compulsive disorder. Other exclusion criteria include current substance use other than nicotine and/or mild to moderate recreational use of cannabis as evidenced by positive urine test; a history of severe head trauma or other severe central neurological disorders (e.g. dementia, Parkinson’s disease, multiple sclerosis); pregnancy or nursing infants; and use of medications or drugs known to interact with the Central Nervous System (CNS) within the last 10 days, with testing at least four half-lives post last intake.

### Power calculations

In order to conduct our effect size calculation two studies were used: Hartwell et al. [28], with an effect size of f = .59 in a study focusing on the anterior cingulate cortex in smokers and Kirsch et al. [39], which investigated heavy social drinkers with an effect size of f = .54 for VS cue-reactivity. Additionally, we examined a study by Tang, Tang, & Posner [50] with an effect size of f = .475 on activation in prefrontal control structures after a mindfulness-based intervention. Since the above-mentioned effect sizes originate from small samples, they might be an overestimation of real effect sizes [9]. Thus, we carefully assume an intermediate effect size of f = .3. We conducted the sample size estimation by means of the G*Power software tool version 3 [19]. The region of interest (VS, 200 voxels) was amended for multiple testing based on Bonferroni correction. As a result of this effect size, we require a sample size of 88 participants to attain a significant effect at *p* < .05 (Bonferroni corrected for multiple testing, region of interest mask of 500 voxels) with a power of 80%. With this sample size of 88 participants, we will be able to identify small effects of f = .15 for our primary clinical outcomes with a power of 95% (group by time interaction).

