### Sample size, group assignment and recruitment

In order to investigate a possible increased ability of our participants to deliberately reduce VS cue-reactivity through the help of MBRP, we will include *N* = 88 participants. These participants will be recruited from inpatients and outpatients of the clinics of the Department of Addiction Behavior and Addiction Medicine at the Central Institute of Mental Health (CIMH) Mannheim, Germany. After inclusion, they will be randomly assigned to four interventional groups (Fig. 1). While all groups will receive rtfMRI NFB from different brain regions, not all groups will be assigned to take part in the mindfulness-based treatment. Two groups will receive treatment as usual (TAU), whereas the other two groups receive MBRP. These two groups (TAU and MBT) will further each be divided in two subgroups, who receive either rtfMRI NFB from the VS with the instruction to down-regulate it (experimental group) or they receive feedback from the control region which is the auditory cortex (control group). The latter area was chosen since it is unrelated to cue-reactivity.

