### Statistical analyses

Offline analyses are conducted with SPM (Wellcome Department of Cognitive Neurology, London, UK) in MATLAB (MathWorks Inc., Sherborn, MA, USA) and include slice-time correction, realignment, segmentation of the anatomical image, normalization to MNI space and smoothing. In our first level analyses, we convolve the time courses with the canonical hemodynamic response function and add them to the General Linear Model (GLM) which also includes 6 movement parameters. The second level analyses comprise correlations with clinical variables and potentially predictive markers for the future course of the disease.

Missing data will be excluded from the analyses. Physiological activity (cardiac and respiratory) will also be recorded and then included in the first level to correct for noise of physiological nature. This will be performed via Global Signal Regression (GSR) and model-based physiology correction [52].

Clinically, the primary outcomes include the number of relapses and the number of days until relapse during the 3-months follow-up. From a neural perspective, the increase of the ability to voluntarily modulate brain activation to alcohol cues after training in the VS serves as a secondary outcome, whereas craving measures such as the Alcohol Abstinence Self-Efficacy Scale [18] will be analyzed as a primary outcome. Another secondary outcome is the influence of combined MBRP and rtfMRI NFB training on functional changes in brain networks of cognitive control (Stop Signal Task (SST), delay discounting).

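### The stated 95% power for f = .15 on the primary clinical outcomes cannot be reproduced from the stated inputs, and the test it names does not fit days until relapse

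*Protocol article*

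**What the plan says.** Under Power calculations, the protocol article sizes the trial on an imaging effect: "Thus, we carefully assume an intermediate effect size of f = .3". The significance level is "Bonferroni corrected for multiple testing, region of interest mask of 500 voxels) with a power of 80" per cent, and so "we require a sample size of 88 participants to attain a significant effect at" that level. An earlier sentence of the same paragraph gives a different mask size: "The region of interest (VS, 200 voxels) was amended for multiple testing based on Bonferroni correction". The software is G*Power 3. The section on sample size and group assignment adds that "they will be randomly assigned to four interventional groups".

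The closing sentence of Power calculations carries the result over to the clinical endpoints: the trial will be "able to identify small effects of f = .15 for our primary clinical outcomes with a power of 95% (group by time interaction"). No alpha, number of groups, number of measurements or correlation accompanies it.

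Statistical analyses then says that "the primary outcomes include the number of relapses and the number of days until relapse during the 3-months follow-up". It adds craving measures as primary, with the AASE as its one named example, and classes voluntary modulation of the ventral striatum as secondary. Table 1 schedules the AASE at baseline and at the third follow-up (FU3) only.

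**The concern.** Two things look wrong.

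- **The size of the figure.** Going from f = .3 to f = .15 cuts the noncentrality to a quarter. Relaxing alpha from .05/500 to .05 recovers part of that loss. It is not obvious that it recovers enough to lift power from 80% to 95% in the same 88 patients.
- **The test.** A group-by-time interaction needs repeated values of the same outcome. The first-named primary outcomes are defined over the follow-up period, and time to relapse has no pre-treatment value.

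This sentence is the only power assurance for the primary clinical outcomes, because N was driven by an imaging measure that the article calls secondary. If the 95% is unsupported, a null clinical result could be read as ruling out a small effect that the trial had much less chance of detecting.

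**Working it through.** **Inputs**

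- From the article: N = 88; four groups; f = .3 with 80% power and a 500-voxel Bonferroni correction (alpha = .05/500 = .0001); f = .15 with 95% power for the clinical claim; AASE at two time points (Table 1).
- Assumed: equal groups of 22, sphericity, no dropout, alpha = .05 for the clinical claim, and the correlation rho, which is varied.

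**Formula** (G*Power, within-between interaction): with k groups and m measurements, lambda = f² × N × m / (1 − rho), df1 = (k − 1)(m − 1), df2 = (N − k)(m − 1). Power comes from the noncentral F distribution.

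**Step 1: rebuild the 88.** With k = 4, m = 2, rho = .5, f = .3 and alpha = .0001:

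- N = 88: lambda = .09 × 88 × 2 / .5 = 31.68, df 3 and 84, power 81.3%.
- N = 84: lambda = 30.24, df 3 and 80, power 77.5%.

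So 88 is the smallest multiple of four that reaches 80%. With 200 voxels the same settings give 80 patients, so 500 is the mask size that matches. That rho = .5 and m = 2 were used is inferred from this match.

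**Step 2: the 95% claim under the same settings.** With f = .15 and alpha = .05: lambda = .0225 × 88 × 2 / .5 = 7.92, df 3 and 84, power **62.7%**. Reaching 95% at rho = .5 would take f of about .23 at N = 88, or N = 196.

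**Step 3: vary the correlation** (four groups, two time points, f = .15, alpha .05):

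| rho | lambda | power |
|---|---|---|
| .3 | 5.66 | 47% |
| .5 | 7.92 | 63% |
| .7 | 13.20 | 86% |
| .78 | 18.00 | 95% |

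A two-group (1 df) contrast at two time points gives 79% at rho = .5 and 95% at rho of about .70. With four groups and rho = .5, the detectable f at 80% power is about .18.

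**Step 4: let the imaging calculation fix rho.** Rho was solved so that 88 patients give exactly 80% in the imaging test, for m = 2 to 5, 1-df or 3-df group tests, and 200 or 500 voxels. Wherever a solution exists, power at f = .15 and alpha .05 is 46% to 69%.

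**Step 5: more measurements.** With four groups and rho = .5, power is 71.4% (m = 3), 79.0% (m = 4) and 84.8% (m = 5). For 95%, four groups need rho of about .73, .68 and .63 respectively. A two-group contrast with five measurements and rho = .5 gives 96.0%.

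**Step 6: relapse outcomes.** For days until relapse, the Schoenfeld approximation suits a two-arm comparison of 44 vs 44: HR = exp[−(1.960 + z) × 2 / √D], with D events and z = .842 for 80% power. The article gives no three-month relapse rate, so D is assumed:

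- a quarter relapse, D = 22: HR about .30
- half relapse, D = 44: exp(−2.802 × 2 / 6.633) = about .43
- three quarters relapse, D = 66: HR about .50

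As a rough cross-check, treating a single-value outcome as normal data gives lambda = .0225 × 88 = 1.98, and power of 18.4% (3 df) or 28.5% (1 df).

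**The case against.** The strongest reply is that the article never says the clinical calculation used the settings inferred for the imaging one. Correlation, measurements and groups are all unstated, and 95% is reachable at f = .15 with 88 patients: four groups at rho of about .78 with two measurements or .68 with four, or a two-group contrast at rho = .5 with five. This stands. A reader might infer that 88 patients cannot deliver 95%; the documents do not support that. They support only that the figure does not follow from what is stated.

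Second, craving measures are named only by example. Table 1 also lists a craving visual analogue scale before and after scanning at MRI 2 to 4, up to six values per patient. With four groups and six measurements, power is 89% at rho = .5 and 96% at rho = .6. So the two-time-point argument holds for the AASE, and for every craving measure only if the analogue scale is not among the primary ones. The article does not say that the 95% refers to that scale.

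Third, relapse is asked about monthly, so the number of relapses could be split by month and given a time factor. That stands too. It is tempting to say that neither relapse outcome has a time dimension. This is firm for days until relapse. The number of relapses is stated as a three-month outcome and would have a time factor only if so split.

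Finally, the 18% and 29% put a count and a time to event on Cohen's f scale. They are rough approximations, not the power of any planned test, and should not be read as the trial's power for relapse.

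**Conclusion.** The point holds in this form: the 95% is not reproducible from the stated inputs. Under the settings that give exactly 88 it is about 63%, a shortfall of some 32 percentage points. For the AASE, 95% requires a within-person correlation of about .78 (four groups) or .70 (two-group contrast), and the article neither states nor argues for such a value. Separately, the named test cannot apply to days until relapse, a primary clinical outcome.

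The 63% rests on an inferred rho of .5, two time points, alpha .05, equal groups and no dropout. It should not be taken as the true power: between rho = .3 and .7 the range is 47% to 86%. Nor does the finding show that the sample size is wrong, since the 88 reproduces for the imaging calculation it was derived from. This is still not a detail to leave to an analysis plan, because the article prints a specific figure and ties it to its primary outcomes.

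**What to change.** Withdraw the 95% sentence and replace it with two statements, leaving N at 88.

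1. **Repeatedly measured primary scale.** Name the scale and state alpha, number of groups, number of measurements and assumed correlation. Show power as a range. For the AASE with four groups, two time points, f = .15 and alpha .05, this is 47% at rho .3, 63% at .5 and 86% at .7, with a detectable f of about .18 at 80% power and rho .5. A bare 63% would repeat the fault of an undocumented assumption.
2. **Relapse outcomes.** Give power or precision on a scale that suits them, for example a detectable hazard ratio of about .43 at 80% power for 44 vs 44, stating the assumption that half relapse (44 events). If the number of relapses is to be analysed by month, say so.

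Describing the clinical comparison as estimation-oriented is optional. The cost is one paragraph of wording and a less favourable stated power; design and sample size do not change.

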**Fig. 1 Fig1:**
[figure not shown]
Flow chart. Flow diagram of the study procedure. *N* = 88 AUD participants will be enrolled in the study. They will randomly be assigned to one of four groups, which differ in terms of MBRP and NFB. All groups will be followed-up monthly for 3 months

Participants assigned to the MBT groups will receive five sessions of MBRP in addition to TAU. In the first MBRP session, the patients receive an introduction to mindfulness. Furthermore, patients are taught to observe their thoughts and emotions with an interest but without judging. These sessions include the SOBER-Breathing training [7] which is a form of therapeutic direction using elements of meditation to reduce craving. In the last session, all relevant topics are repeated. Additionally, all participants in the MBRP group will be instructed to practice the shown mindfulness techniques for at least 15 min per day. After completion, the participants will receive the rtfMRI NFB intervention.

The allocation of the NFB technique (target region or control region) is double-blind. Since it is not possible to blind the patients on their additional treatment in form of MBRP, only the staff conducting the MRI scanning session will not be informed about the received treatment (MBRP or TAU) of the participant, which makes this part of the study single-blind.

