### Baseline assessment

Following the group assignment, participants complete a baseline assessment that begins with a screening session, which determines whether the participants qualify for this study, and includes questionnaires, a neuropsychological assessment and an fMRI session. The questionnaires are focused on demographics, alcohol use, current medication and clinical symptoms. For a comprehensive list of the questionnaires used, please see Table 1. During the neuropsychological assessment, participants perform a dot probe task with alcohol stimuli to assess attentional bias for alcohol [53] and a dimensional card sorting task to measure executive functioning [22]. Then, participants are instructed to set three goals for the intervention. The fMRI session consists of a cue-reactivity paradigm to reflect incentive salience [47], a delay discounting task [21] investigating impulsivity [41] and a stop signal task to assess motor inhibition [23]. Participants who receive MBRP additionally receive an introduction to the program and a short exercise in mindfulness.

**Table 1 Tab1:** Chart of measurements implemented in the study

**Measurement**	S01	MRI 1/baseline	MBRP	MRI 2	MRI 3	MRI 4	MRI5/ Post	FU1/2	FU3
Consent Form for the Study	X								
Sociodemographic Information		X							
Structured Clinical Interview (SKID – I)	X								
Drinking Assessment Interview (Form90)		X							
Urine Sample (Pregnancy & Drugs)	X								
Breath Alcohol Test									X
Current Medication	X								
Current Drug Use	X							X	X
MBRP Confidence Scale				X	X	X			X
MBRP Fidelity Scale			X						
Clinical & Personality Questionnaires	S01	MRI 1/ baseline		MRI 2	MRI 3	MRI 4	MRI5/ Post	FU1/2	FU3
General Depression Scale (Allgemeine Depressionsskala)		X							
Positive and Negative Affect Scale (PANAS)		X							
Perceived Stress Scale (PSS)		X							
Behavioral Inhibition/Approach System (BIS/BAS)		X							
Baratt Impulsiveness Scale (BIS-15)		X							
Fagerstrom Test of Nicotine Dependence (FTND)		X							
Goal Attainment Scaling		X							X
Sensory Inventory		X							
Alcohol-Related Questionnaires	S01	MRI 1/ Baseline		MRI 2	MRI 3	MRI 4	MRI5/ Post	FU1/2	FU3
Quick Drinking Assessment Interview (Form 90)								X	X
Alcohol Dependence Scale (ADS)		X							
Alcohol Abstinence Self-Efficacy Scale (AASE)		X							X
German Inventory of Drinking Situations (DITS-40)		X							
Obsessive Compulsive Drinking Scale (OCDS)		X							X
Alcohol Urge Questionnaire (AUQ)		X							X

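### For the AASE and the other scales taken only at baseline and FU3, the one test named amounts to a change-score comparison; adjusting for the baseline score would be more precise

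*Protocol article*

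**What the plan says.** Under Power calculations, the protocol article says of the clinical outcomes: "we will be able to identify small effects of f = .15 for our primary clinical outcomes". The same sentence gives the power and, in brackets, the test: "for our primary clinical outcomes with a power of 95% (group by time interaction"). It gives no number of visits, number of groups or correlation for this statement.

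Under Statistical analyses, the number of relapses and the days until relapse are the clinical primary outcomes. A later sentence adds that "craving measures such as the Alcohol Abstinence Self-Efficacy Scale [18] will be analyzed as a primary outcome". That section names no model for any clinical outcome.

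Table 1, under Baseline assessment, has a row for the "Alcohol Abstinence Self-Efficacy Scale (AASE") with marks at MRI 1/baseline and FU3 and nowhere else. The OCDS, AUQ and CASA rows carry the same two marks. The craving visual analogue scale is different: it is taken before and after scanning at MRI 2, 3 and 4.

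The text of Baseline assessment places this assessment after group assignment. It also says that patients allocated to MBRP get an introduction and a short mindfulness exercise there. The section on sample size and group assignment says that patients cannot be blinded to MBRP.

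**The concern.** With exactly two visits, the group-by-time F test in a repeated-measures ANOVA is algebraically the one-way ANOVA on the difference FU3 minus baseline. The difference treats baseline as if each unit carried over in full to follow-up. In a randomised comparison with similar variances at both visits, the best slope is rho, which is below 1. Fixing it at 1 adds noise to the comparison. It also over-corrects any chance baseline difference between groups, and such differences are likely with about 22 patients per group.

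What is at stake is precision on a primary outcome whose baseline value is already in the schedule. How much is lost depends on rho.

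**Working it through.** **Inputs**
- N = 88: "we require a sample size of 88 participants" (Power calculations).
- k = 4 groups: "They will randomly be assigned to one of four groups" (Fig. 1 legend). The allocation ratio is not stated; 22 per group is assumed.
- m = 2 visits for AASE, OCDS, AUQ and CASA (Table 1).
- f = .15 (Power calculations).
- Alpha = .05. The article gives this for the imaging test ("a significant effect at *p* < .05"); it is assumed for the clinical test.
- rho: not in the documents. It is assumed, and varied from .3 to .8.

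**Formulas**
- Interaction (change score): lambda = N·m·f²/(1−rho), on (k−1)(m−1) = 3 and (N−k)(m−1) = 84 df.
- With unit variance at both visits, the change score has variance 2(1−rho). The FU3 score adjusted for baseline has residual variance 1−rho². The ratio is 2(1−rho)/(1−rho²) = 2/(1+rho).
- ANCOVA with the same treatment effect: the lambda above times 2/(1+rho), on 3 and 83 df.

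**The plan's own 95%**

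At rho = .5, lambda = 88 × 2 × .0225/.5 = 7.92 and power is 62.7%, not 95%. Four groups and two visits reach 95% only at rho of about .78, where lambda = 3.96/.22 = 18.0. Other settings at rho = .5:
- four groups, four visits: 79.0%
- two groups, two visits: 79.5%
- two groups, four visits: 92.8%
- two groups, five visits: 96.0%

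Only the last is close to 95%, and the AASE does not have five visits.

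**A check on rho = .5**

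The imaging statement (f = .3, "Bonferroni corrected for multiple testing, region of interest mask of 500 voxels) with a power of 80"%) can be run with k = 4, m = 2 and rho = .5. Then lambda = 88 × 2 × .09/.5 = 31.68 and alpha = .05/500 = .0001, which gives 81.3% power. So rho = .5 is a plausible software setting. The same section also mentions 200 voxels, however, and with that number power is 87%. An imaging setting also says little about how stable a questionnaire score is.

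**Comparison for f = .15, N = 88, four groups, two visits**

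| rho (assumed) | lambda, interaction | power, interaction | lambda, ANCOVA | power, ANCOVA | gain (points) |
|---|---|---|---|---|---|
| .3 | 5.66 | 47% | 8.70 | 67% | 20 |
| .4 | 6.60 | 54% | 9.43 | 71% | 17 |
| .5 | 7.92 | 63% | 10.56 | 76% | 14 |
| .6 | 9.90 | 73% | 12.38 | 83% | 10 |
| .7 | 13.20 | 86% | 15.53 | 91% | 5 |
| .78 | 18.00 | 95% | 20.22 | 97% | 2 |
| .8 | 19.80 | 97% | 22.00 | 98% | 1 |

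At rho = .5 the interaction test would need 116 patients to match the ANCOVA with 88. That is 28 more.

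**The case against.** The strongest reply is that the plan has not settled on this model. The interaction appears once, in brackets, in a sample-size sentence. The article is condensed, and an analysis plan that is not shown could specify an ANCOVA. It could also specify a longitudinal model with a common baseline mean, which contains a group-by-time term and has about the same efficiency as ANCOVA. This stands in part: the absence of a covariate from Statistical analyses is no fault in itself. But the interaction is the only between-group test the article names for these outcomes. If another model is intended, the power statement rests on a different one and should be restated.

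The second reply is that the size is unknown. This stands. A reader might infer that the plan costs about 14 points of power, but that figure holds only at rho = .5, which the documents do not give. If the stated 95% is taken at face value for this design, the gain is about 2 points.

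The third reply is about scope, and it also stands. A reader might extend the point to all clinical primary outcomes. The number of relapses and the days until relapse have no baseline value, so there is nothing to adjust for. The craving visual analogue scale has several readings over MRI 2–4 and none at MRI 1, so the two-visit identity does not describe it.

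Finally, a change-score comparison is unbiased over randomisation. The issue is efficiency, not validity.

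**Conclusion.** The point holds for the AASE, and for the OCDS, AUQ and CASA if they are analysed as craving measures. For these, the only test named is a change-score comparison when run as a repeated-measures ANOVA. ANCOVA would do at least as well apart from one degree of freedom. The gain runs from about 20 points of power at rho .3 to about 1 point at rho .8. This assumes equal groups, alpha .05, equal variances at the two visits and no dropout.

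A reader might also infer from the 63% at rho = .5 that the stated 95% is wrong. The documents do not support that much. They leave out the correlation and the number of measurements behind the 95%, and for this design it is reached at rho of about .78. What can be said is that the 95% cannot be reproduced from what is stated, and that the AASE design needs a high correlation to reach it.

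**What to change.** For the AASE, and for the OCDS, AUQ and CASA where they are analysed as craving measures, use a linear model with the FU3 score as response. The terms are the randomised factors (MBRP or TAU, ventral striatum or auditory cortex feedback, and their interaction) and the same scale's MRI 1/baseline score as covariate. Restate the clinical power for this outcome on that model, showing the assumed rho and a range around it.

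Use the baseline score completed before any MBRP exercise. Because the article places baseline after group assignment and patients are not blind to MBRP, state whether allocation was known when the scales were completed. If it was, the covariate could already reflect knowledge of allocation, and the report should say so.

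The analysis change uses scores already scheduled, needs no extra patients or visits, and costs one residual degree of freedom. Obtaining a score before assignment would be a larger step, because it changes the order of the visits as described; the fix does not depend on it.
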